**Interstitial Pneumonitis**

Current phase II and III lapatinib protocols include specific requirements for reporting of signs or symptoms of pneumonitis: subjects who have pulmonary symptoms which are NCI CTC Grade 3 or greater will be removed from study and the events documented as an SAE. As of 03 April 2006, 9 pulmonary events have been reported: 5 subjects experienced interstitial lung disease, 4 subjects experienced pneumonitis. Given the current figure of 3147 lapatinib subjects, this gives an approximate incidence of 0.25% for ‘pneumonitis type’ events. Seven of these events were reported as related to investigational product. Five subjects received lapatinib in combination, and three reports were from lapatinib monotherapy studies. The remaining subject did not receive lapatinib.

Age range for subjects experiencing signs or symptoms of pneumonitis was 48 to 73 years, with a median of 66 years. The majority of the reports (6/9) were for female subjects which may be attributed to the fact that there are a large number of breast cancer subjects in the lapatinib program. Five subjects (55%) who experienced pulmonary events recovered. Three of these 5 subjects required treatment, commonly methylprednisolone or prednisolone. For the remaining four subjects: two events were fatal, one event was ongoing at the time of the subject’s death due to disease progression, and one event was ongoing at the time of reporting. Both subjects who died were participating in monotherapy studies. The first subject died due to interstitial lung disease which the investigator attributed to disease progression. The second subject developed interstitial lung disease and died approximately seven months after the last dose of lapatinib. The subject had recently completed radiotherapy and the investigator felt that lapatinib may have affected the subject’s tolerance to radiotherapy.

Reports of signs/symptoms of pneumonitis are closely monitored and current data do not support the addition of this term to DCSI for lapatinib

**1.3.3.3 Biomarkers**

A Phase 1B trial evaluating tolerability and effects on biomarkers in tumor biopsies in heavily pre-treated patients with metastatic disease expressing EGFR or erbB2 reported that lapatinib was well tolerated at all dose levels tested (500-1600 mg/day) (30). Of 33 evaluable patients, 3 partial responses (PR) (10%) and 12 SD (36%) were reported. An evaluation of tumor biopsies obtained prior to, and after 2-3 weeks of treatment with lapatinib revealed that induction of apoptosis in tumor tissue and inhibition of intratumoral expression of activated Erk1/2, Akt and cyclin D protein appeared to correlate with PR and SD (30). Disease progression was associated with persistent, high levels of expression of these biomarkers. Treatment with lapatinib was not effective when insulin growth factor receptor (IGFR) was highly expressed (31). Tumor types in which objective response or stable disease were seen included: breast (7), colorectal (2), ovarian (2), lung (1), granular cell (1), and head and neck (1) carcinomas as well as adenocarcinoma of unknown primary (1). Objective responses were observed in ErbB2-expressing breast cancer patients who had progressed after receiving prior trastuzumab (Herceptin™)-based regimens. The most common adverse events included grade 1-2 rash (25%), diarrhea (27%), and nausea/vomiting (21%).

**1.3.4 Clinical Pharmacokinetics**

The pharmacokinetics of lapatinib are similar in healthy volunteers and patients, demonstrating oral absorption that is incomplete, highly variable, and sometimes delayed. After dosing, plasma concentrations rise to a peak at approximately 4 h and thereafter decline with measured half-lives averaging up to 14 h. However, accumulation with daily dosing achieves steady state in 6-7 days, which suggests a true elimination half-life on the order of 24 h. Administration of the same daily dose in a BD schedule results in 2‑fold greater systemic exposure than a OD schedule. Despite this inconsistency, systemic exposure generally increases with increasing dose. Absorption is increased by ingestion with food. Elimination of lapatinib is predominantly through metabolism by CYP3A4/5 with negligible renal excretion. Significant changes in systemic exposure to lapatinib result from co-administration of drugs that are potent inhibitors or inducers of CYP3A.

**1.4 Rationale for this Study**

HER2 (ErbB2), a member of the ErbB2 family of receptors, is expressed in 15-30% of primary breast cancers and its expression is associated with aggressive biological behaviour and poor disease outcome (22, 23). Breast cancer has been also shown to express high levels of EGFR and hormone-resistant disease is associated with an increased expression of both EGFR and EGFR ligands (32).

CTCs are identified in a significant proportion of patients with breast cancer both in early and metastatic disease (12, 16). The initial detection as well as the persistence of CTCs after the completion of systemic adjuvant treatment is associated with worse prognosis (12-14). Similarly, in the metastatic setting, the level of CTCs soon after the initiation of systemic treatment is a poor prognostic indicator (16). CTCs have been identified as malignant cells and at least theoretically bear the potential of giving rise to overt metastatic disease. In line with this, targeted-therapies such as monoclonal antibodies, have been proposed as alternative modalities capable of eliminating micrometastatic tumour cells resistant to prior chemotherapy or hormonal therapy (33).

HER2 expression has been demonstrated in occult tumor cells present in the bone marrow and/or the systemic circulation in 60% of breast cancer patients (34, 35). The expression of HER2 in CTCs is an independent prognostic factor for reduced survival (35). EGFR expression has been also demonstrated in circulating breast cancer cells by RT-PCR (36). The expression of both HER-2 and EGFR on CTCs has been confirmed by immunofluorescence microscopy (37). Both EGFR and HER-2 receptors influence many aspects of tumour cell biology including growth, survival, metastasis and angiogenesis. Selective inhibition of these growth factor receptors located on micrometastatic cells could theoretically interrupt the cellular signal transduction cascade leading to cell survival and subsequent development of metastatic disease.

The principal mechanism by which HER2 transmits signals is the formation of heterodimeric receptor complexes with EGFR, HER-3 or HER-4. It has been suggested that HER-2, being the most common heterodimerization partner of EGFR, may play an important role in the oncogenic activity of EGFR. In turn, EGF stimulation of EGFR, leads to activation of HER2 by heterodimerization (38). Thus, combined inhibition of both EGFR and HER2 may be more efficacious than targeting either one of them alone. Lapatinib is a selective reversible inhibitor of both EGFR and HER2 tyrosine kinases that inhibits receptor phosphorylation and downstream PI3K/Akt and MAP kinase signalling pathway in cells overexpressing EGFR or HER-2 (24, 25). Lapatinib has been shown to exert both antiproliferative and pro-apoptotic effects against breast cancer and represents an ideal candidate to be used for the elimination of circulating breast cancer cells. The feasibility of this approach has been demonstrated by the administration of trastuzumab in patients with breast cancer that resulted in the elimination of circulating cells in 22 out of 30 patients (33).

A significant amount of data point to the presence of CTCs in the peripheral blood of patients with solid malignancies as a prognostic indicator of poor clinical outcome (39). However, besides the clear prognostic value of CTCs, it is not yet known whether additional treatment targeting CTCs that persist despite systemic treatment, will translate into a benefit in progression-free and/or overall patient survival. At least theoretically, patients could benefit from a secondary treatment aiming in eliminating micrometastatic disease. This treatment could be tailored on the basis of the molecular profile of CTCs which reflect the subset of tumor cells that is potentially capable of giving rise to overt metastatic disease. This approach could be applicable either in the adjuvant and/or the metastatic disease setting.

Lapatinib is considered a novel and promising agent in the treatment of human breast cancer. Based on the above data, it could be very important and clinically relevant to know if lapatinib is capable of eliminating occult tumour cells circulating in the blood of breast cancer patients.

# 2. Study objectives

In the present study we would like to evaluate the efficacy of lapatinib in eliminating chemo- and/or hormone- resistant tumour cells circulating in the blood of patients with breast cancer.

- 1. **Primary objective**

The efficacy of lapatinib on HER2-positive CTCs will be measured by quantitative analysis of circulating tumour cells in the blood before, during and after the completion of lapatinib treatment. These cells will be detected by immunofluorescence microscopy on cytospins prepared from peripheral blood mononuclear cells (PBMCs) isolated by ficoll-hypaque density gradient centrifugation.

**2.2 Secondary objectives**

# 1. Correlation of the levels of CTCs with response to treatment

2. Assessment of the safety of lapatinib administration in this patient population

2.3. Exploratory Objectives

- Detection of cytokeratin-positive cells by immunofluorescence microscopy
- Detection of cytokeratin-positive/EGFR- positive CTCs (immunofluorescence microscopy)

# 3. Study plan and procedures

Patients will receive lapatinib monotherapy 1500 mg/day for a period of at least 1 month (unless disease progression occurs at an earlier time point). Blood samples will be collected at study entry, prior to the first dose and subsequently every month. Tumor assessment by imaging studies will be performed prior to study entry and subsequently every three months. At the end of the first month period patients with will be assessed for the presence of CTCs in their peripheral blood. Patients with decreased or stable CTC counts will continue treatment and will be assessed every month. Patients with increased CTC counts will be withdrawn from the study if further increase is documented at re-assessment after the second treatment course. In subsequent cycles, treatment will be also discontinued in case of two consecutive increases in CTC values. Moreover, treatment will be discontinued in case of disease progression, occurrence of unacceptable toxicity or consent withdrawal, irrespectively of CTC counts.

##

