**Efficacy**

- **Primary outcome variable**:
- Effect of lapatinib on HER2-positive CTC counts.
- **Secondary outcome variables:**
- Correlation of the kinetics of CTCs with response to treatment
- Safety of lapatinib treatment in this patient population

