Completed Monotherapy Study EGF20008(27) was conducted in female subjects with advanced (Stage IIIb) or metastatic (Stage IV) breast cancer refractory to treatment with anthracycline-, taxane- and capecitabine-containing regimens. Subjects enrolled in Cohort A had ErbB2 overexpressing tumors and were refractory to treatment with trastuzumab-containing regimens. Subjects enrolled in Cohort B had ErbB2 non-overexpressing tumors and had no prior treatment with trastuzumab. Table 2 presents a summary of the efficacy results for the primary/secondary endpoints of overall response rate and clinical benefit rate using RECIST criteria. The independent review was independent of subject management and blind to the response evaluations of the investigator review.

A total of seven subjects in Cohort A had a positive tumor response (CR or PR) based on either independent panel or investigator review. A statistical analysis of time to tumor response and duration of tumor response was not conducted due to an insufficient number of responders. Of the seven subjects who had a response, first response was documented at Week 4 (Day 29) for one subject, Week 8 for five subjects (Days 50-57), and Week 16 (Day 113) for one subject. The duration of response ranged from 55 to >250 days (8 to >36 weeks).

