**Table 2. Overall Response Rate and Clinical Benefit Rate, Study** **EGF20008**

|  | **Lapatinib 1500mg QD** | | | |
| --- | --- | --- | --- | --- |
|  | **Cohort A**  **N=140** | | **Cohort B**  **N=89** | |
| **Overall Response Rate,**  **n (%)** | **Independent Review** | **Investigator Review** | **Independent Review** | **Investigator Review** |
| **Best Response** |  |  |  |  |
| Complete Response (CR) | 0 | 3(2) | 0 | 0 |
| Partial Response (PR) | 2 (1) | 3 (2) | 0 | 0 |
| Stable Disease | 46 (33) | 38 (27) | 10 (11) | 10 (11) |
| Progressive Disease | 64 (46) | 85 (61) | 49 (55) | 76 (85) |
| Unknown | 28 (20) | 11 (8) | 30 (34) | 3 (3) |
| Tumor Response Rate | 1,4% | 4,3% | 0% | 0% |
| Clinical Benefit Rate1 | 5,7% | 5,7% | 0 | 0 |
| Clinical Benefit Rate2 | 15,7% | 10,7% | 1,1% | 1,1% |

1. Defined as CR or PR or Stable Disease ≥24 weeks

2. Ad-hoc analysis defined as CR or PR or Stable Disease ≥16 weeks

The median time to tumor progression was 9.1 weeks in Cohort A and 7.6 weeks in Cohort B based on independent review. The median time to tumor progression was 8.1 weeks in Cohort A and 7.0 weeks in Cohort B based on investigator review.

The median progression-free survival interval was 9.1 weeks in Cohort A and 7.6 weeks in Cohort B based on independent review. The Kaplan-Meier estimated probability of being progression-free at 4 months and at 6 months was 34% and 18%, respectively, in Cohort A, and 7% and 0%, respectively, in Cohort B.

The median survival time was 29.4 weeks for subjects in Cohort A and 18.6 weeks for subjects in Cohort B.

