## Table 4. Study design and flow chart

| **SCREENING PERIOD DAY -21 to 0**  Patient informed consent; past medical history; demography; tumour assessment (chest X‑ray, computerised tomography [CT] scan and bone scan), CTCs assessment (double staining immunofluorescence microscopy for HER2/cytokeratin) |
| --- |
|  |
| **MAIN TREATMENT PERIOD (1 MONTH)**  Patients evaluated for concurrent illness/therapy; physical examination, adverse events at all visits (every month)  Every month: haematology; biochemistry; tumour assessment, CTCs assessment (double staining immunofluorescence experiments)  At 3 months (or at any time in case of suspected clinical disease progression): chest X‑ray, computerised tomography [CT] scan and bone scan) |
|  |
| **SECOND TREATMENT PERIOD**  Patients evaluated for concurrent illness/therapy; physical examination, adverse events at all visits (every month)  Every month: haematology; biochemistry; tumour assessment, CTCs assessment (double staining immunofluorescence experiments)  Every 3 months (or at any time in case of suspected clinical disease progression): chest X‑ray, computerised tomography [CT] scan and bone scan)  . |

Table 5 STUDY PLAN

| Study plan | Screening | Start of treatment | Treatment | | | | | | Discontinuation |
| --- | --- | --- | --- | --- | --- | --- | --- | --- | --- |
| Day (or week) | -21 to  -7 | **0** | +4we | +8we | +12we | +16 we | +20 we | +24 we |  |
| Visit | V1 | V2 | V3 | V4 | V5 | V6 | V7 | V8 |  |
| Informed consent | X |  |  |  |  |  |  |  |  |
| Medical history | X |  |  |  |  |  |  |  |  |
| Pregnancy test (if appropriate) |  | Xa |  |  |  |  |  |  |  |
| Inclusion/exclusion criteria | X | X |  |  |  |  |  |  |  |
| Physical examination including Vital signsb / Performance Status / weight |  | X | X | X | X | X | X | X | X |
| Concurrent medication |  | Xc | X | X | X | X | X | X | X |
| ECG |  | X |  |  |  |  |  |  |  |
| Clinical chemistry/ Hematologyb |  | X | X | X | X | X | X | X |  |
| Tumour assessment | X |  |  |  | X |  |  | X |  |
| CTCs assessment (CTCs number, double staining immunofluorescence microscopy | X | X | X | X | X | X | X | X | X |
| Adverse eventsc |  |  | X | X | X | X | X | X | X,de |
| Dispense study medication |  | X | X |  |  | X |  |  |  |
| Survival |  |  |  |  |  |  |  |  | Xf |

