#### 3.3.3.2 Procedures for discontinuation

#### Subjects who discontinue should, if possible, be seen and assessed by an investigator(s). The reason for discontinuation and the date of discontinuation must be documented on the case report form (CRF). If possible any diary cards, questionnaires (e.g. for Quality of Life assessments) and investigational products should be returned by the subject.

All subjects who have new or worsening CTC grade 3 or 4 laboratory values at the time of discontinuation must have further tests performed and the results recorded on the appropriate CRF until the laboratory values have returned to CTC grade 1 or 2, unless these values are not likely to improve because of the underlying disease. In these cases, the investigators must record their opinions on the CRFs and in the subject’s medical records. Laboratory abnormalities should not be reported as adverse events unless any criterion for an SAE is fulfilled, the laboratory abnormality causes the subject to discontinue from the study, or the investigator insists the abnormality should be reported as an AE.

At discontinuation all on-going study-related toxicities and SAEs must be followed until resolution, unless in the investigator’s opinion, the condition is unlikely to resolve due to the subject’s underlying disease.

After discontinuation from treatment, subjects must be followed up for all existing and new AEs for 30 calendar days after the last dose of study drug. All new AEs occurring during that period must be recorded (if SAEs they must be reported within 24 hours) and followed up for resolution as above.

Any subject who withdraws from study treatment for reasons other than progression should continue, where possible, to have objective tumour assessments every 8 weeks in order to collect information on progression of disease.

When disease progression has been documented, the long-term follow up information for survival should be collected at least every 8 weeks by telephone contact with the subject, subject’s family, or by contact with the subject’s current physician.

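### The tumour-assessment calendar behind the CTC–response outcome is inconsistent between sections and changes with a patient's CTC course

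*Protocol*

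**What the plan says.** The synopsis lists as a secondary outcome: "Correlation of the kinetics of CTCs with response to treatment". Section 2.2 has a matching objective. Table 5 schedules CTC counts every 4 weeks.

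For tumour assessment the protocol gives three calendars:

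- Section 3: "Tumor assessment by imaging studies will be performed prior to study entry and subsequently every three months". Table 5 matches this, with marks at screening, week 12 and week 24 and none at weeks 4 or 8 or in the discontinuation column.
- Table 4, both treatment periods: "Every month: haematology; biochemistry; tumour assessment, CTCs assessment (double staining immunofluorescence experiments". The three-monthly X-ray, CT and bone scan form a separate line, which opens in the first period with "At 3 months (or at any time in case of suspected clinical disease progression". The method of the monthly item is not stated, although the screening row of the same table uses the term for those three imaging examinations.
- Section 3.3.3.2: patients who stop treatment for a reason other than progression "should continue, where possible, to have objective tumour assessments every 8 weeks".

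Under section 3, a patient whose CTC count rises at month 1 leaves if a further rise is found after the second course. Section 3.3.3.1 lists two consecutive rises as a reason for discontinuation.

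Section 1.3.3.1 supplies progression times on lapatinib monotherapy. For EGF20008: "The median time to tumor progression was 9.1 weeks in Cohort A and 7.6 weeks in Cohort B based on independent review".

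**The concern.** A correlation between CTC course and tumour response can be interpreted only if the tumour is read on a schedule that does not depend on the CTCs. Here it does. Rising CTCs end treatment, and ending treatment changes the scan interval. The patients with the clearest adverse CTC signal can leave with no scheduled on-treatment scan at all, and Table 5 requires none when they leave. Their tumour reading is then taken off treatment and at different dates from everyone else's. Part of any difference in response between CTC groups would come from the calendar and not from the disease.

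A second problem affects all patients. Between baseline and week 12 the only imaging is on suspected clinical progression, in an open-label trial whose staff must act on the CTC count each month. A progression in that window is either dated by someone's suspicion or carried forward to week 12. CTC changes at weeks 4 and 8 then have no systematic tumour reading of similar date.

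**Working it through.** The protocol gives no calculation for this outcome, so there is no planned figure to reproduce. Response is taken here to mean tumour response or progression by RECIST, the criterion named in the synopsis.

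**Step 1. Same disease course, two calendars.** Take two patients who progress silently at the same time and are found only by scheduled scans. Patient A has stable or falling CTCs and stays on treatment, with scans at weeks 12 and 24. Patient B has rises at weeks 4 and 8 and leaves at week 8, with scans at 8 + 8 = 16 and 16 + 8 = 24. The protocol does not say whether the 8 weeks run from withdrawal or from the start of treatment. For an exit at week 8 both give weeks 16 and 24; whether a scan is also due at week 8 itself is unclear.

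| True progression | A recorded at | B recorded at | B minus A |
|---|---|---|---|
| After week 8, to week 12 | 12 | 16 | 4 weeks later |
| After week 12, to week 16 | 24 | 16 | 8 weeks earlier |
| After week 16, to week 24 | 24 | 24 | none |

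The recorded dates differ by up to 8 weeks for identical disease, and the sign depends on when progression occurs. The net direction of the bias therefore cannot be fixed in advance. Nor can its size, because the protocol gives no expected proportion of patients leaving under the CTC rule.

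**Step 2. Share progressing before the first scheduled scan.** Inputs are all eight medians in section 1.3.3.1. With exponential progression (an assumption), the share progressed by week 12 is 1 − 0.5^(12/median). The last column is the binomial probability that more than 10 of 20 patients progress by then.

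| Source | Median (weeks) | Share by week 12 | Expected of 20 | P(more than 10 of 20) |
|---|---|---|---|---|
| EGF20008 Cohort B, investigator | 7.0 | 0.695 | 13.9 | 0.947 |
| EGF20008 Cohort B, independent | 7.6 | 0.665 | 13.3 | 0.906 |
| EGF20008 Cohort A, investigator | 8.1 | 0.642 | 12.8 | 0.862 |
| EGF20002, investigator | 9.0 | 0.603 | 12.1 | 0.764 |
| EGF20008 Cohort A, independent | 9.1 | 0.599 | 12.0 | 0.753 |
| EGF20002, independent | 15.3 | 0.419 | 8.4 | 0.169 |
| EGF20009, 500 mg BID (PFS) | 15.7 | 0.411 | 8.2 | 0.151 |
| EGF20009, 1500 mg QD (PFS) | 17.0 | 0.387 | 7.7 | 0.104 |

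Week 12 is later than five of the eight medians and earlier than three.

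**Step 3. Check on the exponential shape.** The protocol also gives 4-month (17.4-week) progression-free estimates. For EGF20008 the exponential predicts 26.6% in Cohort A against 34% stated, and 20.5% in Cohort B against 7% stated. For EGF20002 (independent review) it predicts 45.5% against 41%. The shape is only rough. Log-linear interpolation between the median and the 4-month value in EGF20008 gives:

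- Cohort A: ln S(12) = ln 0.5 + ln(0.34/0.5) × (12 − 9.1)/(17.4 − 9.1), so S = 0.437 and 56% have progressed.
- Cohort B: the same with 0.07 and 7.6, so S = 0.207 and 79% have progressed.

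The conclusion that a large share may progress before week 12 does not hang on the exponential form.

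**The case against.** The strongest reply is that imaging at weeks 12 and 24 is stated consistently in section 3 and Table 5, that the interval is a design preference in a 20-patient pilot, and that the 8-weekly rule governs a different phase and so contradicts nothing. As wording, the last part is fair. It does not remove the problem, because the CTC count can decide which phase a patient is in, and the outcome compares patients by CTC course. The off-treatment assessments are also only where possible.

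On Table 4, the monthly item is listed apart from the three-monthly imaging, so it may well mean a clinical assessment. That is plausible, but the table does not say so and Table 5 has no such row. If it does mean imaging, the week-12 concern falls and section 3 and Table 5 are wrong instead.

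Several stronger readings are tempting and are not supported:

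- A reader might infer that most patients will progress before the first scan. That holds for five of the cited medians but not for 15.3, 15.7 or 17 weeks. EGF20008 also enrolled patients refractory to anthracycline, taxane and capecitabine regimens, whereas inclusion criterion 5 here requires response or stable disease on previous treatment.
- A reader might infer that response in most patients rests on suspicion-triggered scans. The shares above count progressions, not triggered scans. A silent progression in a patient still under assessment is found at week 12, only late.
- A reader might take it that week 12 misses responses, since in EGF20008 "first response was documented at Week 4 (Day 29) for one subject, Week 8 for five subjects (Days 50-57". Those responses lasted at least 55 days. One first seen on day 50 would run to day 105, and one first seen on day 29 to day 84, which is week 12.
- A reader might say that a CTC rise is a written trigger for imaging. It is not: the trigger is suspected clinical progression. That known counts could influence suspicion is a possibility, not a rule of the plan.

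**Conclusion.** The point stands as one of inconsistency and CTC-dependent ascertainment. The protocol gives three different tumour-assessment calendars, and its own CTC rule moves patients from one to another, in some cases before any scheduled on-treatment scan. Scheduled detection dates can then differ by 4 to 8 weeks between CTC groups with identical disease. The net bias in the correlation cannot be quantified from the document.

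Separately, about 39% to 70% of patients may progress before the first scheduled scan, depending on which cited median applies. This assumes exponential progression, that the cited medians transfer to this population, and that Table 4's monthly entry is not imaging. The consequence concerns a secondary outcome; the CTC counts of the primary outcome are not affected.

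The figures do not establish that any particular interval is the right one. With a first scan at week 8, 46% to 55% would still have progressed beforehand on medians of 9.1 and 7.0 weeks, and 30% on 15.3 weeks. Because progression ends treatment, the choice of interval also affects clinical management and is for the sponsor.

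**What to change.** Reconcile section 3, Tables 4 and 5 and section 3.3.3.2 into one tumour-assessment calendar, counted from the start of treatment and the same on and off treatment, whatever the CTC course. The sponsor chooses the interval in view of the cited progression times. State whether Table 4's monthly entry is clinical or imaging, and make Table 5 agree. Record for each progression whether it came from a scheduled or an unscheduled scan. Analyse progression timing as interval-censored, or add a sensitivity analysis limited to scheduled scans; the statistical analysis plan, not at hand, may already provide for this.

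The cost is a short amendment, one data field and possibly a small change in scan numbers. To week 24, a patient leaving at week 8 without progression has two scheduled scans after leaving on either calendar (weeks 16 and 24, or weeks 12 and 24). If the sponsor instead chose the 8-week interval throughout, patients who stay progression-free on treatment would have three scans by week 24 (weeks 8, 16 and 24) in place of two. The CTC discontinuation rule need not change.
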